### Intervention

The ProLife programme is a complex behavioural intervention aimed at improving treatment outcomes in TB patients who smoke tobacco, drink alcohol at harmful or hazardous levels, or do both. The ProLife programme has been developed in line with the Medical Research Council (MRC) guidance on developing and evaluating complex interventions [35] and has undergone a period of development and feasibility testing in South Africa. The paper reporting the results of this evaluation has not yet been published. The conceptual framework used to develop the ProLife programme assumes that smoking cessation, reducing harmful alcohol use and improved adherence to TB and HIV treatment will result in improved TB treatment outcomes.

Participants randomised to the intervention arm will receive three brief MI counselling sessions, lasting 15–20 min, each one month apart, from a trained LHW at their TB clinic. In the initial MI session, occurring at the start of TB treatment, the counsellor will establish the participant’s tobacco smoking habits and problem drinking; potential obstacles and facilitators for medication adherence or treatment initiation (both TB treatment and ART) will be determined. The participant will determine which factor should be prioritised (i.e. agenda setting), which could be a plan either to quit tobacco smoking, reduce or quit drinking or deal with barriers relating to ART or TB medication adherence. For participants who are HIV-infected and not yet on ART, beliefs and attitudes regarding HIV-testing or ART will be explored to facilitate ART initiation and adherence. The second session will build on the previous one and will focus on the previous agenda before moving on to the next behavioural problem (tobacco, alcohol or medication adherence) where applicable. The third session will deal with the last identified problem.

The individual counselling sessions will be re-enforced with SMS text messages regarding information, motivation and behaviours (IMB) supporting tobacco cessation, alcohol use and medication adherence. Text messages will be delivered twice a week over 12 weeks. All participants will first receive 10 TB-related messages. These messages will be followed by seven alcohol or smoking-related messages depending on whether the participant smokes or drinks. Co-joint users will receive all sets of messages (i.e. 24 in total).

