### Participants

The inclusion criteria for participants are:adult patients (aged ≥ 18 years) with drug-sensitive (bacteriologically or clinically confirmed) PTB;initiating TB treatment or on TB treatment for < 1 month (these include both ‘new’ and ‘retreatment’ patients);current smokers and/or hazardous/harmful drinkers who are not alcohol dependent (Alcohol Use Disorders Identification Test [AUDIT] score ≥ 8 for men or ≥ 7 for women but < 20);access to a functional mobile phone; andunderstands one of the four languages used for the trial (Sesotho, Setswana, Isizulu or English).

Exclusion criteria:alcohol-dependent participants (AUDIT score ≥ 20);Extrapulmonary TB without PTB; orResistance to one or more TB drugs at baseline (because drug-resistant TB needs further investigations which take several months and is treated through a long, specialised treatment programme if present).

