Individual TB treatment records will be used as the primary source of information. The TB treatment record is the routinely used clinical document initiated by the TB nurse when the patient first presents at the TB clinic and includes demographic information as well as a comprehensive overview of the patient’s treatment over time. The TB treatment outcomes will be obtained 6–9 months after the TB treatment start dates. This is to allow for short periods of treatment interruption and time needed to confirm the TB treatment outcomes status. For example, the TB nurse may have to wait for end of treatment TB sputum or culture results or time may be required to determine whether a participant died. In some cases, TB patients may also undergo a longer TB treatment regimen.

Routinely reported outcomes will be verified for correctness by checking the actual individual diagnosis and treatment records. For example: if the outcome is classified as cured, then the criteria for diagnosis and outcome definitions should have been adhered to. Attempts will be made to verify the information of patients classified as ‘defaulted’ or who are lost to follow-up by contacting them telephonically or sending them a short text message. Sputum cultures and smears will be performed at baseline, two months, three months and six months per routine care.

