### Secondary outcomes

The following outcome measures will also be recorded at the six-month follow-up:sputum conversion at the end of treatment: this will be measured by negative culture or smears in the group of participants who had bacteriology confirmed PTB at baseline, i.e. cure rates in intervention group versus control group for participants who initially had sputum AFB-positive, culture-positive or GeneXpert-positive PTB;six-month continuous smoking abstinence: the Russell Standard defines continuous abstinence as a self-report of not smoking > 5 cigarettes from the start of the abstinence period (in this case, six months), supported by a negative biochemical test (exhaled carbon monoxide [CO] < 10 ppm) at final follow-up [39]. For the purpose of our study, we will, however, use a more stringent criterion of exhaled CO < 7 ppm, based on findings from our previous study that some participants who reported continued smoking had an exhaled CO < 10 ppm [26]. This analysis will be performed on the group of participants who were current tobacco smokers at baseline;reduction in harmful or hazardous drinking: alcohol use will be measured using the AUDIT questionnaire. The questionnaire will be administered at screening (which will take place on the same day or shortly after the baseline assessment) and again at three months and six months. Changes in the total AUDIT score will be used to compare change in drinking behaviour between control and intervention groups. This analysis will be performed on the group of participants who were harmful or hazardous drinkers at baseline.TB and ART medication adherence: adherence to both TB and ART medications will be measured using a modified version of the AIDS Clinical Trials Group (ACTG) Adherence Questionnaire. The questionnaire is a validated tool for measuring adherence specifically to ART and we will use an adapted version to also measure TB medication adherence [40]. Field workers will administer the baseline part of this questionnaire as part of the baseline CRF and adherence will be measured at both three months and six months.

Adherence will be measured using an adherence index calculated by the formula (using the four-day recall table):$$ \left[\mathrm{Total}\ \mathrm{number}\ \mathrm{of}\ \mathrm{doses}\ \mathrm{taken}/\mathrm{Total}\ \mathrm{number}\ \mathrm{of}\ \mathrm{doses}\ \mathrm{prescribed}\right]\ \mathrm{x}\ 100 $$

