ART patients with at least 95% of adherence will be considered as having optimal adherence and those with < 95% will be considered as having low (or suboptimal) adherence. For the TB medication regimen, patients with at least 95% of adherence will be considered as having optimal adherence and those with < 95% will be considered as having low (or suboptimal) adherence:increase in proportion of HIV-positive participants on ART: HIV status will be recorded in the TB Treatment Record. HIV-positive participants will be asked about ART status at baseline, three months and six months using standardised questions on the CRF.

The following outcomes will be measured at three months:biochemically verified three-month sustained tobacco cessation;reduction in harmful or hazardous drinking;TB drug and ART adherence;increase in proportion of HIV-positive participants on ART.

The schedule for enrolment, intervention and assessments is presented in Fig. 2. Table 2 summarises the methods of data collection and analysis for each of the primary and secondary outcomes.

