### Data collection and management

Data will be collected and recorded by field workers equipped with Android phones with a mobile data collection application installed. MI counselling and data collection will take place in a well-ventilated private area inside or outside the clinic (but within the grounds of the health facility); MI sessions will be audio-recorded where consent has been obtained. Fieldworkers and LHWs will be provided with high particulate respirator masks to minimise the risk of infection.

Fieldworkers will follow-up all participants in both arms at three and six months within a window period of two weeks before and two weeks after the ideal three-month and six-month visit. Participants will receive SMS reminders three days before each planned visit. Participants will also be in a position to send ‘please call me’ messages to the district coordinators, who will then call the participant to solve problems that may have arisen with the appointment.

The electronic data captured will be stored on secured and password-protected storage servers and mobile phones which ensure data privacy through only allowing authorised research staff access to the data. The electronic data collection system used for the study requires an SMS gateway to send and receive messages to the research participants. Consenting participants’ phone numbers, participant IDs and associated SMS messages will be stored on the SMS gateway’s secured and password-protected server.

Data quality will be ensured by providing fieldworkers with standard operating procedures (SOPs), training and ongoing support on the importance of data quality, data collection and data collection problem solving. Training will consist of a four-day session before the commencement of the pilot and a one-day training session focusing on problems identified during the pilot preceded the trial. The data manager will continuously monitor the captured data for missing variables and inconsistencies in order to resolve any data problems.

The data manager will export the data from the secured server, conceal the participants study arm allocation and de-identify the data before sharing the data in STATA and R compatible formats. The exported de-identified data will be stored in Dropbox, a secure cloud storage platform, for sharing with the lead trial statistician at the University of York for analysis.

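### Six-month TB adherence uses a four-day recall index that has no denominator once TB treatment has ended, so the six-month arm comparison rests on a group partly selected after randomisation

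*Protocol article*

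**What the plan says.** Under Secondary outcomes, the protocol fixes the measure: "Adherence will be measured using an adherence index calculated by the formula (using the four-day recall table"), the formula being total doses taken over total doses prescribed, times 100. On timing, "adherence will be measured at both three months and six months". The result is then split in two: "For the TB medication regimen, patients with at least 95% of adherence will be considered as having optimal adherence", and anything lower is low adherence. There is no category for a participant who is no longer prescribed TB drugs.

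Four other places determine where the six-month visit falls relative to treatment:

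- Participants (inclusion criteria): "initiating TB treatment or on TB treatment for < 1 month".
- Data collection and management: follow-up takes place "within a window period of two weeks before and two weeks after the ideal three-month and six-month visit". The section does not say whether the months run from enrolment or from the start of TB treatment.
- Secondary outcomes: end-of-treatment sputum conversion is listed among the six-month measures. In Table 1, the local cure definition uses a late sputum result at 23 weeks.
- Primary outcome: treatment outcomes are read 6–9 months after treatment start. Of this window the protocol says "This is to allow for short periods of treatment interruption"; it also cites time to confirm the outcome and, in some cases, longer regimens.

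In Table 2, every other outcome row names its analysis population. The adherence row gives only a binary adherent/non-adherent outcome.

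**The concern.** The protocol treats about six months as the end of a standard TB course, yet asks at six months what share of the last four days' prescribed doses was taken. For a participant who has finished, nothing was prescribed in those days, and the formula has no value.

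The loss is not random. Whether someone still has TB doses prescribed at that visit depends on whether treatment was interrupted, was prolonged, or was still running because the visit came early. These events follow randomisation and are tied to adherence, which the intervention aims to change. If the intervention helps people finish on time, it removes good adherers from its own denominator. Multiple imputation, which the Statistical analysis section offers for missing data, does not help: adherence to doses that were never prescribed is not a missing quantity.

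Adherence is a stated objective and a link in the intervention's conceptual framework, so a misleading six-month result would affect how the trial is interpreted.

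**Working it through.** The protocol gives no figure for the adherence outcome, so there is none to reproduce. The check is how often the index is undefined.

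**Inputs from the protocol.** Time on treatment at enrolment, L: 0 to under one month (taken as 0–30 days). Visit deviation, W: −14 to +14 days. Recall: 4 days.

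**Assumptions.** Course length D: 168 days (24 weeks), 182 days, or six months at 30.4375 days = 182.6 days (183 below). W is uniform. L is uniform over the range shown.

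**Formula.** Days from treatment start to visit: t = L + 182.6 + W. The index is 0/0 when t − 4 ≥ D. For D = 182.6 this means W ≥ 4 − L, so the share is (10 + L)/28, capped at 1.

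- L = 0 (enrolled on day one, or visit counted from treatment start): 10/28 = 36%.
- L over 0–7 days (mean 3.5): 13.5/28 = 48%.
- L over 0–14 days (mean 7): 17/28 = 61%.
- L over 0–30 days: the share reaches 1 at L = 18, giving [(10×18 + 18²/2)/28 + 12]/30 = 24.2/30 = 81%.

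Share of on-time participants with a zero denominator:

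| Lag at enrolment | D = 183 | D = 182 | D = 168 |
|---|---|---|---|
| none | 36% | 38% | 88% |
| 0–7 days | 48% | 50% | 97% |
| 0–14 days | 61% | 63% | 99% |
| 0–30 days | 81% | 82% | 99% |

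The even spread of visits matters. If every visit fell exactly at six months, the share would be 0% with no lag and a 182–183 day course, and 100% with a 168-day course.

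**Three-month visit.** The latest time from treatment start is 91.3 + 14 + 30 = 135 days. This is before day 168, so completing treatment cannot empty that denominator.

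**Can the sign change?** Illustration with assumed values. Let on-time completion be 86% v 76%, borrowing the success rates in the Sample size section. Let completers be 95% adherent and control non-completers 50%. Let the 10 points moved to completion come from non-completers who were 70% adherent. The remaining intervention non-completers are then (24×0.50 − 10×0.70)/14 = 35.7% adherent. Assume all non-completers keep a value.

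- Everyone observed: 0.86×0.95 + 0.14×0.357 = 86.7% v 0.76×0.95 + 0.24×0.50 = 84.2%, a difference of +2.5 points.
- 36% of completers without a value: 0.573/0.690 = 83.0% v 0.582/0.726 = 80.1%, +2.8 points from unrounded values.
- 80% without a value: 0.2134/0.312 = 68.4% v 0.2644/0.392 = 67.5%, +0.9 points.
- 90% without a value: 0.1317/0.226 = 58.3% v 0.1922/0.316 = 60.8%, −2.5 points.

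With a fraction k of completers keeping a value, the arms are equal when 0.0298k = 0.0048, that is k = 0.16. In this example the sign turns once more than about 84% of completers have no value.

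**The case against.** A reader might infer that most participants have finished treatment by the six-month visit, and that only those with interrupted or longer regimens still have a value. The protocol supports neither as a general statement. It gives no treatment length as a number and no starting point for the visit. The 23-week sputum is a time point in a cure definition, not a stated end of treatment. Under Recruitment process, screening follows immediately on the nurse's starting treatment, which suggests that short lags are common; the one-month limit is a maximum. With a 182–183 day course and visits spread over the window, 18% to 64% of on-time participants keep a valid index, mainly those enrolled at treatment start and seen early.

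The adapted questionnaire, the case report form (Additional file 2) and the assessment schedule (Fig. 2) are not shown. They might restrict the TB items to those on treatment, or ask about the last days of treatment. The first would make the selection explicit without removing it. The second would remove the zero denominator, but the article's definition does not say so. An analysis set can also be left to the analysis plan.

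What stands is this: formula, recall period, time point and cut-off are fixed in the article and together give no value for a share of participants that is substantial once visits spread over the window. That is a stated rule that works badly, not only detail left for elsewhere.

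**Conclusion.** The point holds for one time point of one secondary outcome. As defined, six-month TB adherence cannot be computed for participants who finished more than about four days before the visit. Assuming a 168–183 day course and visits spread over the permitted window, that is about 36% of on-time participants if visits run from treatment start or enrolment is on day one. It is about half if enrolment falls within a week and the course is 182–183 days, and 80–99% if enrolment is spread over a month or the course is 168 days.

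The participants left are partly selected by post-randomisation events related to adherence, so the arm comparison can be biased. A reader might infer that the result will reverse; that is not shown. In the illustration the bias is small and upward at the low end of the range, shrinks the difference at 80%, and reverses it only above about 84%. All of this rests on assumed adherence rates.

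Three-month TB adherence and the primary outcome are unaffected. The end of TB treatment has no bearing on ART adherence either.

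**What to change.** Make three months the time point for the between-arm comparison of TB medication adherence, in all randomised participants, and count those who have defaulted by then as non-adherent. Report six-month TB adherence descriptively only, among participants still prescribed TB drugs, and show by arm how many were no longer on treatment. State whether the three- and six-month visits are counted from enrolment or from the start of TB treatment.

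Use a whole-course measure in place of the three-month index only if the TB treatment record holds dose or attendance data. The protocol describes that record as an overview of treatment over time, but does not say that such data are recorded or extracted.

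The cost is the loss of the six-month TB adherence comparison. No extra visit or data collection is needed, because the three-month measurement is already planned.

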**Fig. 2 Fig2:**
[figure not shown]
SPIRIT Figure outlining data collection throughout trial

**Table 2 Tab2:** Summary of methods of data collection and analysis for primary and secondary outcomes

Variable	Method of data collection	Method of data analysis
Primary outcome: TB treatment outcome as defined by WHO and the South Africa TB Management Guidelines (see Table 1)	• CRF and TB treatment record • Treatment outcome as recorded by TB nurses in TB cards using the standard WHO definitions of cure, completions, failure, death, TB treatment interruption, drug resistance developed in course of treatment (confirmed for correctness by checking sputum culture/smear at baseline, at 5 and 6 months)	Binary outcome: successful (cured of completed) vs not successful (died, failure, treatment interruption, drug-resistant TB) All participants, excluding those transferred out
Secondary outcome: sputum conversion	• Sputum culture/smear at baseline, 5 and 6 months to determine cure rates for PTB patients who had a positive smear or culture at baseline • Sputum conversion at 2–3 months	Binary cured vs not cured for the subgroups of participants who had a positive smear/culture at baseline Binary conversion vs not for the subgroups of participants who had a positive smear/culture at baseline
Secondary outcome: change in smoking behaviour	• CRF – questions as per Russell’s Standard – baseline smoking behaviours and then at 3 and 6 months • Exhaled carbon monoxide reading at 3 and 6 months	Binary outcome validated 3 and 6 months sustained smoking cessation for the subgroup of participants who were smoking at baseline
Secondary outcome: percentage reduction in harmful or hazardous drinking (change in AUDIT score)	• AUDIT score at baseline and at 3 and 6 months	Change in AUDIT score (continuous) for subgroups of participants who were hazardous or harmful drinkers at baseline
Secondary outcome: HIV and TB medication adherence	• CRF – questions modified from ACTG	Binary outcome (% adherent vs non-adherent)
Secondary outcome: proportion of HIV-positive participants on ART	• HIV status at baseline • ART status at baseline, 3 months and 6 months	Binary on ART vs not on ART for the subgroup of HIV-positive participants, taking into account baseline % on ART

### Data collection and management

Data will be collected and recorded by field workers equipped with Android phones with a mobile data collection application installed. MI counselling and data collection will take place in a well-ventilated private area inside or outside the clinic (but within the grounds of the health facility); MI sessions will be audio-recorded where consent has been obtained. Fieldworkers and LHWs will be provided with high particulate respirator masks to minimise the risk of infection.

Fieldworkers will follow-up all participants in both arms at three and six months within a window period of two weeks before and two weeks after the ideal three-month and six-month visit. Participants will receive SMS reminders three days before each planned visit. Participants will also be in a position to send ‘please call me’ messages to the district coordinators, who will then call the participant to solve problems that may have arisen with the appointment.

The electronic data captured will be stored on secured and password-protected storage servers and mobile phones which ensure data privacy through only allowing authorised research staff access to the data. The electronic data collection system used for the study requires an SMS gateway to send and receive messages to the research participants. Consenting participants’ phone numbers, participant IDs and associated SMS messages will be stored on the SMS gateway’s secured and password-protected server.

Data quality will be ensured by providing fieldworkers with standard operating procedures (SOPs), training and ongoing support on the importance of data quality, data collection and data collection problem solving. Training will consist of a four-day session before the commencement of the pilot and a one-day training session focusing on problems identified during the pilot preceded the trial. The data manager will continuously monitor the captured data for missing variables and inconsistencies in order to resolve any data problems.

The data manager will export the data from the secured server, conceal the participants study arm allocation and de-identify the data before sharing the data in STATA and R compatible formats. The exported de-identified data will be stored in Dropbox, a secure cloud storage platform, for sharing with the lead trial statistician at the University of York for analysis.

All research data and documents referring to the ProLife trial will be stored and maintained in a secured storage space at SMU for a minimum of 15 years from the end of the ProLife trial. Study materials will be destroyed 15 years after the study.

